**Methods/design:**

This cluster randomized controlled trial aims to enroll 70 physicians of chiropractic (unit of randomization) to either passive or active surveillance system to report adverse events that occur after treatment for 60 consecutive pediatric (13 years of age and younger) patient visits (unit of analysis). A modified enrollment process with a two-phase consent procedure will be implemented to maintain provider blinding and minimize dropouts. The first phase of consent is for the provider to confirm their interest in a trial investigating the safety of chiropractic manual therapy. The second phase ensures that they understand the specific requirements for the group to which they were randomized.

Percentages, incidence estimates, and 95% confidence intervals will be used to describe the count of reported adverse events in each group. The primary outcome will be the number and quality of the adverse event reports in the active versus the passive surveillance group. With 80% power and 5% one-sided significance level, the sample size was calculated to be 35 providers in each group, which includes an 11% lost to follow-up of chiropractors and 20% of patient visits.

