## Methods

### Study design

The study design is a pragmatic, superiority, cluster randomized clinical trial with a modified enrollment process to maintain participant blinding. DCs in private practice who treat children will be the unit of randomization with random allocation in a 1:1 ratio to active or passive surveillance reporting systems. Cluster randomization was chosen for practical reasons with the unit of analysis being reports from the individual chiropractic patient visits. The University of Alberta’s Research Ethics Board reviewed and approved this study (Pro00027903). The trial has been registered at ClinicalTrials.gov (NCT02268331). The study protocol was prepared using the Standard Protocol Items: Recommendations for Interventional Trials (SPIRIT) guidelines [16] (see Additional file 1) and also the “Methods” section of the Consolidated Standards of Reporting Trials (CONSORT) 2010 Checklist for reporting a cluster randomized controlled trial [17] (see Additional file 2).

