### Recruitment, randomization, and enrollment

Licensed DCs in the United States and Canada will be recruited from a variety of venues, including pediatric chiropractic-specific events and organizations, social media, and professional newsletters/magazines. Word of mouth and referrals from colleagues and past participants will also be source of referral into the study.

As shown in Fig. 1, DCs interested in the study will complete a demographic questionnaire and review/sign the initial consent document, which states that they are interested in enrolling in a study to report safety information from 60 consecutive pediatric visits. They will then be randomized to passive or active surveillance by the study coordinator ([name]). To promote baseline equivalence, we will stratify by DC’s self-reported average proportion of pediatric patients seen (>20% versus ≤ 20%). To maintain allocation concealment, the REDCap (Research Electronic Data Capture) Randomization Module will be utilized with a random, variable, permuted block size, generated by an independent biostatistician [18]. Interested DCs will have study materials sent directly to their offices. This material includes the Consent Form that gives details on the surveillance system to which they were randomly assigned. DCs are considered enrolled in the study after that Consent Form is signed and they complete the online baseline survey, which collects additional demographic data and assesses patient safety attitudes [19]. Throughout study participation, to ensure compliance with study methods, regular communications will occur via email or telephone between the study coordinator ([name]) and the DC.

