### Outcomes

The primary outcome will be the number (the count) and quality (i.e., ability to meaningfully interpret/adjudicate, a binary variable) of the DC’s adverse event(s) reports per patient visit and per patient in each group. Quality of adverse event reports will be assessed by the adjudicators’ ability to meaningfully adjudicate the report (section above).

A secondary outcome is the change in patient safety attitudes for participating DCs. This will be measured in both groups using the Safety Organizing Scale [19], which is a nine-item survey with a 7-point rating scale (1 – “Not at all”; 7 – “To a very great extent”). This questionnaire is to be completed at two time points: at baseline (the online baseline survey prior to study enrollment) and after adverse event data collection is complete for each participating DC. In the active surveillance arm, additional variables to assess adverse events and associated factors for adverse events include: patient-reported adverse events, manual therapy treatment description, patient health history, and patient satisfaction [22].

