### Statistical methods

The count of reported adverse events (any severity) in each group will be expressed with percentages and incidence estimates, and their 95% confidence intervals (CIs). The primary analysis will compare the cumulative incidence of adverse event reports in active versus passive surveillance. Because the outcome is number of events, it is assumed that the data will follow a Poisson distribution. Hence, a Poisson regression with log links will be used in general estimating equation (GEE) analyses with an appropriate sandwich estimator to take into account the DC cluster correlation. Groups will be compared using an intention-to-treat analysis.

Sensitivity analysis, using the same GEE analyses as above, will be conducted for reports that were not adjudicated (because of uninterpretable adverse events) and differences in how missing data were handled (i.e., imputing using average incidence and highest incidence). The binary variable expressing if the quality of the adverse event report allowed for meaningful interpretation/adjudication will be evaluated using the McNemar’s exact test because of the expected rarity of reports and cluster correlation.

Secondary analysis will address differences in the count of adverse event reports by patient-only, provider-only, and those reported by the active surveillance versus the provider-reports in the passive surveillance. Like the primary analyses, Poisson regression with log links will be used in GEE analyses to account for cluster-specific methods. Patient safety attitudes will be measured before and after participation and compared across surveillance groups.

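### Report quality, part of the primary outcome, is assigned McNemar's exact test, a paired-data test, although the two arms are independent, unmatched groups of DCs

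*Protocol article*

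**What the plan says.** The Abstract gives the primary outcome as the "number and quality of the adverse event reports in the active versus the passive surveillance group". The Outcomes section repeats both parts. Besides the number of reports it lists "quality (i.e., ability to meaningfully interpret/adjudicate, a binary variable) of the DC’s adverse event(s) reports per patient visit and per patient in each group", and adds: "Quality of adverse event reports will be assessed by the adjudicators’ ability to meaningfully adjudicate the report". The study hypothesis predicts better quality reporting in the active arm.

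On design, DCs are the "unit of randomization with random allocation in a 1:1 ratio to active or passive surveillance reporting systems" (Study design). Under Recruitment, randomization, and enrollment, "we will stratify by DC’s self-reported average proportion of pediatric patients seen" (above 20% versus 20% or less), using a "random, variable, permuted block size, generated by an independent biostatistician". No crossover and no matching of DCs, visits or reports is described.

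In Statistical methods, the count is analysed by Poisson GEE with a sandwich estimator for the DC cluster. The quality variable "will be evaluated using the McNemar’s exact test because of the expected rarity of reports and cluster correlation".

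**The concern.** McNemar's test asks whether two yes/no readings on the same or matched units differ, and it uses only the discordant pairs. In this trial the active and passive reports come from different DCs, different visits and different events. Stratified permuted-block allocation balances the arms but does not match members of one arm to members of the other.

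The two stated reasons do not supply the missing pairs. Rarity is a reason for an exact or permutation test, and such tests exist for independent groups. Several reports from one DC are clustered within an arm. That is not pairing across arms, and McNemar's test makes no allowance for it. The count outcome in the same section does get a between-group method that handles clustering.

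At stake is the quality half of the hypothesis. Its test would either be uncomputable, because there are no pairs, or be computed on a table or a pairing that does not measure the difference in quality.

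**Working it through.** **1. The plan's own figure.** Inputs from Sample size: reporting rates 4.3% (active) and 0.53% (passive), ICC 0.13, 60 visits per DC, 5% one-sided, 80% power, losses of 11% of DCs and 20% of visits.

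- Two proportions, pooled variance, no continuity correction: 204 visits per arm before clustering.
- Visits per DC after loss: 60 × 0.80 = 48.
- Design effect: 1 + (48 − 1) × 0.13 = 7.11.
- DCs per arm: 204 × 7.11 / 48 = 30.2, so 31. Then 31 / 0.89 = 34.8, so 35.

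The stated 35 per arm reproduces. It concerns the report rate, not quality.

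**2. Expected reports, all severities, after losses.** Active: 31 × 48 × 0.043 = 64.0. Passive: 31 × 48 × 0.0053 = 7.9, about 8.

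**3. Reading A: the test is put on the arm-by-quality table.** The off-diagonal cells are the non-adjudicable active reports (b) and the adjudicable passive reports (c). The exact p-value is 2 × P(X ≤ min(b, c)) with X ~ Binomial(b + c, 0.5). If the true quality is q in both arms, the expected cells are b = 64(1 − q) and c = 8q. These are equal only when 64(1 − q) = 8q, that is at q = 64/72 = 0.89. At any other q the test sees an apparent difference that comes from the report counts.

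Example with q = 50% in both arms: 32/64 and 4/8 adjudicable, so b = 32 and c = 4. McNemar gives p = 0.0000019. Fisher's exact test on the same table gives p = 1.0.

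Rejection rates by exact enumeration, two-sided 5%, equal quality, no clustering:

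| Assumed quality, both arms | McNemar, 64 vs 8 | Fisher, 64 vs 8 | McNemar, 32 vs 4 | McNemar, 16 vs 2 |
|---|---|---|---|---|
| 50% | 100% | 2.2% | 98% | 58% |
| 70% | 81% | 3.2% | 33% | 6.5% |
| 80% | 14% | 2.2% | 3.2% | 0.6% |
| 90% | 0.5% | 1.9% | about 0% | about 0% |

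The quality values are assumptions, because the protocol gives none. The two right-hand columns are there because the Adjudication section sends only moderate, severe or serious events to the experts. The number of reports with a quality rating is therefore probably below 64 and 8, by a share that the protocol does not state.

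The test also misses real differences. With 90% (active) versus 50% (passive) and 64 vs 8 reports, McNemar rejects in 3% of trials and Fisher in 71%. Fisher's test is only a benchmark here, since it too ignores clustering.

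If report counts and quality are both simulated with ICC 0.13, the McNemar false-positive rates are 93%, 45% and 25% at q = 50, 80 and 90%. The increase at 80% and 90% comes from the variation that clustering adds to the counts.

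**4. Reading B: reports are paired arbitrarily across arms.** At most 8 pairs can be formed, so 64 − 8 = 56 active reports are dropped. With equal quality the two-sided rejection rate is 0.4% at q = 50%, 0.2% at 70% and about 0.002% at 90%. Power for 90% versus 50% is 7% two-sided, or 21% one-sided.

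**5. What a cluster-level test has to work with.** Simulating beta-binomial counts with 31 DCs, 48 visits, rate 0.53% and ICC 0.13, the passive arm has a median of 2 DCs with any report (5th to 95th percentile 0 to 5). It has at most one in about 32% of trials and none in about 9%. Restriction to moderate or worse events lowers these numbers further.

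**The case against.** The strongest reply is that the high false-positive rates rest on a guess about use. The protocol does not say that the arm-by-quality table would be entered into McNemar's test, and under arbitrary pairing the test is conservative. The rates also rest on quality values that the protocol does not give, and on all reports rather than the adjudicated ones. At 80% quality with 64 vs 8 reports, the expected cells (about 13 vs 6) give p = 0.17. All of this stands. A reader might infer that the plan will almost certainly declare a false difference in quality; the documents do not support that.

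A reader might also infer that the trial's main result has no valid test. That is not supported either. Statistical methods says that the primary analysis compares the cumulative incidence of reports, and the sample size rests on report rates alone.

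A third reply is that the pairing could be between adjudicators, or between caregiver and DC on the same active-arm visit. The protocol describes no such pairing for this outcome, and neither would compare active with passive surveillance.

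Nor can the point be left to an analysis plan that is not shown. The protocol names the test and gives its rationale, so a plan that followed it would inherit the mismatch.

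Finally, a cluster-respecting replacement will have little data in the passive arm. That is correct, and it shapes the fix.

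**Conclusion.** The point holds as a mismatch between test and design. A paired test is fixed for a comparison between independent, unmatched arms, for an outcome that the protocol names as part of the primary outcome, and neither stated reason justifies it. This conclusion needs no assumption about quality or report numbers.

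The numerical consequence does depend on assumptions. On the arm-by-quality table with equal quality and unclustered reports, false positives run from about 100% (50% quality) to 0.5% (90% quality) at 64 vs 8. At 70% quality they fall from 81% to 33% at 32 vs 4 and to 6.5% at 16 vs 2. Under arbitrary pairing the test is conservative and discards most of the active reports. In neither case does it answer the quality question. The correction should be made before analysis.

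**What to change.** In Statistical methods, replace the McNemar sentence with a comparison of the proportion of adjudicable reports between independent groups that respects DC clusters. One suitable form permutes arm labels over DCs within the two randomisation strata and reports the difference with a DC-level interval (cluster bootstrap or cluster-robust).

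Add two statements:

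- If too few passive-arm DCs submit an adjudicated report, quality will be reported descriptively with intervals and not tested. Set the threshold before the data are seen.
- The comparison is limited to DCs who reported, which is a post-randomisation condition expected to differ by arm, so it should be interpreted with that in mind.

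A McNemar-type test can be kept for data that really are paired, such as caregiver and DC reports on the same active-arm visit.

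The cost is a few sentences and a few lines of code. No new data are needed, and randomisation, the count analysis and the sample size do not change.

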Other planned secondary analyses are designed to identify factors associated with adverse events from the data gathered in the active surveillance group. Potential factors for adverse events include patient characteristics (e.g., age, presenting condition, sex, health history), provider characteristics (e.g., years in practice, specialty training), and treatment provided (e.g., high-velocity, low-amplitude or other). With the adverse event reports categorized by their severity (i.e., none, mild, moderate, severe, serious), logistic regression analyses will be used to model factors associated with the adverse events. If the number of moderate, severe, and serious events are small, the outcome will be dichotomized as any adverse event versus no adverse event. If numbers of moderate, severe and serious events are sufficiently large, multivariable polytomous logistic regression will be used.

Planned exploratory analyses include: (1) subgroup analysis for providers with a specialty pediatric certification and number of reported adverse events (i.e., the primary outcome); (2) assessment of the feasibility to implement a surveillance system within chiropractic offices from individual provider feedback; and (3) review of debrief interview to gain insight into participating DCs’ overall thoughts on the study, including barriers to implementation, perceived benefit of participating, and being blinded to intervention. An assessment of bias will be conducted with responding and non-responding patient demographic characteristics for the active surveillance group. All analyses will be conducted using Stata version 13 (StataCorp LP, College Station, TX, USA).

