### Sample size

An estimated active surveillance reporting rate of 4.3% and intracluster correlation of *ρ* = 0.13 were based on a pilot study of a similar active surveillance used within the chiropractic profession in Canada [20, 21]. We assumed a passive surveillance reporting rate of 0.53%, based on prior academic literature [8]. A one-sided significance level was utilized as it seems reasonable to believe that passive surveillance will result in under-reporting of adverse events [23]. We calculated that a sample size of 35 providers in each group, with each DC collecting data from 60 pediatric patient visits, and 5% one-sided significance level, would lead to 80% power. This includes an anticipated loss to follow-up of 11% of DCs and 20% of patient visits.

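### The active-arm risk-factor models are specified with no stated allowance for clustering by chiropractor; fitted as written, intervals for provider-level factors would be much too narrow

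*Protocol article*

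**What the plan says.** The Statistical methods section of the protocol article plans secondary analyses to "identify factors associated with adverse events from the data gathered in the active surveillance group". Patient, provider and treatment factors are listed; the second group is "provider characteristics (e.g., years in practice, specialty training"). On the model, the text says that "logistic regression analyses will be used to model factors associated with the adverse events". If the moderate, severe and serious events are few, the outcome becomes any event versus none; if they are numerous enough, "multivariable polytomous logistic regression will be used". Neither sentence names GEE, a random effect, a robust variance or the DC as a cluster.

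The paragraphs just before do name it. The primary Poisson GEE is to be fitted "with an appropriate sandwich estimator to take into account the DC cluster correlation". The sensitivity analyses reuse that GEE. Cluster correlation is given as one reason for the test of report quality. For the secondary counts: "Like the primary analyses, Poisson regression with log links will be used in GEE analyses to account for cluster-specific methods". No sentence extends cluster adjustment to all analyses.

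The Sample size section bases its calculation on "An estimated active surveillance reporting rate of 4.3% and intracluster correlation of" 0.13, both taken from a pilot of similar active surveillance.

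**The concern.** Visits to the same DC are correlated, and the plan puts a figure on that correlation. A logistic model that treats visits as independent takes its precision from the number of visits. For a factor that is constant within a DC, the information comes mainly from the number of DCs, of whom about 31 are expected to remain in the active arm. This is the kind of covariate for which ignoring clustering does most harm, and the plan lists such covariates explicitly.

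These analyses would support statements about whether a provider's experience or specialty training is associated with adverse events in children. The Discussion presents the study as the largest prospective evaluation of its kind, so such statements may carry weight. With independence standard errors, an apparent provider-level association could often be no more than ordinary variation between DCs.

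**Working it through.** **Inputs from the Sample size section.** Active rate 4.3%; passive rate 0.53%; ICC 0.13; 35 DCs per arm; 60 visits per DC; one-sided 5% level; 80% power; loss of 11% of DCs and 20% of visits. Retained visits per DC: m = 60 × 0.80 = 48.

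**Step 1: reproduce the plan's own figure.** The two-proportion formula (pooled variance under the null, no continuity correction, one-sided 5%, 80% power) gives 204 independent visits per arm. The design effect is 1 + (m − 1) × ICC = 1 + 47 × 0.13 = 7.11. DCs needed: 204 × 7.11 / 48 = 30.2, rounded up to 31. Allowing for 11% loss: 31 / 0.89 = 34.8, rounded up to 35. This matches the stated number, so the plan's sample size is consistent with this degree of clustering.

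**Step 2: effect on a provider-level factor under independence.** For a covariate constant within a DC, the variance is understated by the design effect DE, so the standard error is too small by √DE. A nominal two-sided 95% interval then covers 2Φ(1.96/√DE) − 1. The 0.13 is the plan's value. The values 0.05 and 0.02 are assumptions, to show what happens if covariates absorb much of the between-DC variation.

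| ICC | DE, 48 visits | √DE | Coverage | DE, 60 visits | √DE | Coverage |
|---|---|---|---|---|---|---|
| 0.13 | 7.11 | 2.67 | 54% | 8.67 | 2.94 | 49% |
| 0.05 | 3.35 | 1.83 | 72% | 3.95 | 1.99 | 68% |
| 0.02 | 1.94 | 1.39 | 84% | 2.18 | 1.48 | 82% |

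At 48 visits, the matching false-rejection rates of a two-sided 5% test are about 46%, 28% and 16%. The plan states no test level for these models, so that level is an assumption.

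**Step 3: check by simulation.** Beta-binomial data were simulated with event rate 4.3%, a binary provider factor with no true effect, and 2,000 runs per setting.

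- ICC 0.13, over 31 or 35 DCs and 48 or 60 visits: the true spread of the estimate was 2.6 to 2.9 times the independence standard error, and coverage was 49% to 56%. A cluster-robust variance with t on (number of DCs − 2) degrees of freedom gave about 92%.
- ICC 0.05, 31 DCs, 48 visits: ratio 1.82, independence coverage 73%, cluster-robust 95%.
- ICC 0.02, 31 DCs, 48 visits: ratio 1.40, independence coverage 84%, cluster-robust 94%.

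The simulation agrees with the formula. It also shows that a simple robust variance still falls somewhat short at ICC 0.13 with this few DCs.

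**Step 4: information available.** Expected active-arm events after losses: 31 × 48 × 0.043 = 64. For a provider-level factor at ICC 0.13 these are worth about 64 / 7.11 = 9 independent events. With no losses: 35 × 60 × 0.043 = 90, worth about 90 / 8.67 = 10.

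**The case against.** The strongest reply is that the text is silent, not wrong. It names a regression family and no variance estimator, and logistic regression is compatible with GEE, clustered variance or a DC random effect. The article condenses a fuller plan that is not shown, and it recognises DC clustering in the design, the sample size and the other analyses. A reader might infer that the trialists chose to treat visits as independent. The documents do not support that: nothing says the models are unadjusted, and an analysis plan could supply the adjustment.

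That limits the wording but does not remove the point. The article does specify the model here, and it mentions clustering for each neighbouring comparison of reports between the arms. It then moves to another model family and stops mentioning it. Someone following the text would have no instruction to adjust.

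Two further limits stand. First, 0.13 comes from a pilot and need not be the residual ICC after covariates, which is unknown; hence the range down to 0.02. Second, a reader might extend the result to treatment techniques or patient characteristics. The calculation covers only factors constant within a DC. For factors that vary within a DC the error is smaller and may go in either direction, and it has not been quantified here.

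**Conclusion.** The point holds as a conditional one. The protocol specifies logistic or polytomous regression for the active-arm risk factors and states no allowance for DC clustering. If the models are fitted as written, standard errors for provider-level factors would be too small by a factor of about 2.7 at the plan's ICC and 48 visits per DC, and by about 1.4 at an assumed residual ICC of 0.02. Even at that low value, a 95% interval would cover only about 84%.

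This assumes an independence fit, a covariate constant within a DC and roughly equal visits per DC. It would be too strong to say flatly that null provider associations will be declared about half the time: that needs all of these conditions, the full ICC of 0.13 and a two-sided 5% rule. The analyses are secondary and within one arm, so the comparison of active with passive surveillance is untouched. The change should still be made, because the error could be large and the correction is cheap.

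**What to change.** State that the risk-factor models account for clustering by DC. Suitable choices include a logistic GEE or a DC-clustered robust variance for the dichotomous outcome, and a DC-clustered variance for the polytomous model; other estimators would also serve. Add a small-sample correction, and test provider-level factors on degrees of freedom based on the number of DCs (about 31), not the number of visits.

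This needs a sentence or two and no new data, and it follows the approach already stated for the count analyses. The cost is wider intervals: for provider-level factors, about 2.7 times wider than under independence at ICC 0.13 and 48 visits. Some provider-level questions may then prove unanswerable with the events expected.
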